**Methods:**

This is a feasibility randomized controlled trial. We plan to recruit a total of 36 community-dwelling older adults using purposive sampling. Participants will be randomized 1:1 to either the intervention or the control group. The intervention group will be asked to engage with KOKU-Nut 3 times a week for 12 weeks. Participants in the control group will receive a leaflet promoting a healthy lifestyle. All study participants will complete questionnaires at baseline and the end of the 12 weeks. A sample of participants will be asked to participate in an optional interview. The study will collect a range of data including anthropometry (height and weight), dietary intake (3-day food diary), physical function (grip strength and 5-times sit-to-stand), perceived quality of life (EQ-5D), usability (System Usability Scale), and safety (adverse events).

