### Interventions

Participants in the intervention group will be helped to download KOKU-Nut onto their iPad or tablet during the baseline visit. The researcher (CF) will demonstrate the features and assist with any technical queries. In cases where participants do not have the necessary devices or data to join the intervention, a tablet with KOKU-Nut installed will be provided for the duration of the intervention. Participants will be asked to engage with KOKU-Nut at least 3 times a week throughout the 12-week period. This will involve carrying out strength and balance exercises and engaging with the gamification features relating to bone health and healthy eating. A crib sheet and contact details for the research team will be available if participants require additional support to help with technical issues.

Participants assigned to the control group will continue with usual care and receive a leaflet developed by Age UK about the importance of a healthy lifestyle including information on the importance of staying active and nutrition [19]. This will allow the comparison of a more traditional way to provide lifestyle advice compared to the digital health tool.

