Secondary outcomes will consider the usability and safety of the intervention and the practicality of collecting and assessing the effectiveness of KOKU-Nut compared to an information booklet about healthy living. The perceived usability of KOKU-Nut will be assessed using the validated 10-item system usability scale. Responses are measured on a 5-point Likert scale ranging from 1 (strongly disagree) to 5 (strongly agree). A score >68 is considered above-average usability and >80 is considered high usability such that participants are likely to recommend the product to peers. The safety of the intervention will be based on the number of adverse events that occurred as a result of participation in the study. We will consider the practicality of collecting effectiveness data by documenting the amount and rationale for any missing data. Changes in means and SDs will be compared to consider the preliminary effectiveness of the intervention and to calculate sample sizes for a future trial. The study will be assessed against progression criteria based on Shanyinde et al [21] to determine progression to a powered RCT. Figure 1 shows the schedule of the intervention and assessment according to the SPIRIT statement.

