### Sample Size

As this is a feasibility study that is not designed to detect statistically significant differences in measures, no formal power calculation has been conducted to determine the sample size. Lancaster et al [22] recommend a sample size of 36 participants for feasibility and pilot studies, so after accounting for potential dropout (at 20%), we aim to recruit 18 participants in each arm.

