### Allocation

Randomization will be undertaken by a separate member of the research team using the Sealed Envelope randomization service [24], and participants will be stratified by age group (65-75 years and 76 years and older), gender, and prior experience of using a tablet or iPad. Given the nature of the intervention, participants and researchers will be unblinded.

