### Ethical Considerations

Ethics approval was obtained from The University of Manchester Research Ethics Committee on August 18, 2023 (2023-17372-30569) to ensure that adequate safeguards are in place to protect the privacy of participants and to maintain the confidentiality of data. This study will be conducted in accordance with the UK Policy Framework for Health and Social Care Research and the Declaration of Helsinki guidelines. Prior to data collection, all the participants who agreed to participate in the study will sign a consent form, which includes a description of the study, its objectives, and participants’ involvement and rights (Multimedia Appendix 1). Participation in the study is entirely voluntary and participants can withdraw at any time. Participants will not receive financial compensation for their contribution to the study. Any deviations from the protocol will be put through the appropriate ethical amendment process. It is not anticipated that the study will be stopped prior to its intended end date. However, the study will be halted if safety issues arise regarding the intervention or resources to conduct the study are no longer available. Outcomes will be disseminated through conference presentations and publications in peer-reviewed journals in deidentified form. The findings will also be shared through presentations with digital inclusion teams and community stakeholders.

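### The safety outcome counts only adverse events caused by participation, so the count rests on a causal judgement that is likely to differ between the arms

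*Protocol article*

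**What the plan says.** Safety is one of the stated secondary aims. The protocol article describes its measure in two ways.

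- Abstract, Methods: among the data to be collected are "usability (System Usability Scale), and safety (adverse events", with no restriction by cause.
- Methods, Outcomes: "The safety of the intervention will be based on the number of adverse events that occurred as a result of participation in the study". Only events caused by participation enter the outcome.

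Three other statements bear on how the second definition would work.

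- Allocation: "Given the nature of the intervention, participants and researchers will be unblinded".
- Interventions, on what the app arm is asked to do: "This will involve carrying out strength and balance exercises and engaging with the gamification features relating to bone health and healthy eating", at least three times a week for 12 weeks. On the comparator: "Participants assigned to the control group will continue with usual care and receive a leaflet developed by Age UK".
- Ethical Considerations: "the study will be halted if safety issues arise regarding the intervention".

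The article does not say who decides whether an event resulted from participation. Falls appear in the Introduction as a risk that exercise can reduce, but they are not named as a safety outcome.

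**The concern.** The Outcomes definition applies a causal test first and counts second. For a single fall or strain in a person aged 65 or older, cause can seldom be settled from the event itself. What normally settles it is the randomised control arm, which shows how many such events occur without the app. Counting only attributed events sets that reference aside.

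The causal test is also unlikely to work alike in the two arms. One arm is asked to exercise regularly; the other receives usual care and a leaflet. Someone who knows the allocation has an obvious candidate cause in the first arm and very little in the second. The count then reflects how readily events are attributed as well as how often they occur. It can show an excess that does not exist or hide one that does. Safety is a stated aim and the results are meant to inform a powered trial, so a count of this kind would be a weak basis for saying that the app is safe.

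**Working it through.** The article gives no adverse event rate, safety threshold or power, so there is no stated figure to reproduce. The main check is textual; the arithmetic only shows direction and scale.

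**Textual check.** The Abstract wording includes every adverse event. The Outcomes wording includes only those resulting from participation. A fall judged unrelated is inside the first definition and outside the second, so the two are not equivalent.

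**Inputs.** Arm size: "we aim to recruit 18 participants in each arm" (Sample Size). Assumed, because the document gives none: the 12-week risk of an event in each arm, at most one event per participant, and the probability that an event is attributed to participation.

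**Formulas.** Expected events = 18 × risk. Expected counted events = 18 × risk × attribution probability.

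| Assumed risk, app / control | All events, app / control (difference) | Attribution, app / control | Counted, app / control (difference) |
|---|---|---|---|
| 5% / 5% | 0.90 / 0.90 (0) | 25% / 0% | 0.23 / 0 (0.23) |
| 10% / 10% | 1.80 / 1.80 (0) | 25% / 0% | 0.45 / 0 (0.45) |
| 10% / 10% | 1.80 / 1.80 (0) | 50% / 0% | 0.90 / 0 (0.90) |
| 10% / 10% | 1.80 / 1.80 (0) | 50% / 10% | 0.90 / 0.18 (0.72) |
| 20% / 10% | 3.60 / 1.80 (1.80) | 0% / 0% | 0 / 0 (0) |
| 20% / 10% | 3.60 / 1.80 (1.80) | 25% / 0% | 0.90 / 0 (0.90) |
| 20% / 10% | 3.60 / 1.80 (1.80) | 50% / 0% | 1.80 / 0 (1.80) |
| 20% / 10% | 3.60 / 1.80 (1.80) | 50% / 10% | 1.80 / 0.18 (1.62) |

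Example: 18 × 0.10 × 0.25 = 0.45.

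When nothing is attributed in controls, the counted difference equals the true one only if the share attributed in the app arm matches the share truly caused by the app. That share is 0% with equal risks and (20 − 10)/20 = 50% when the risk doubles. Elsewhere the attribution rate sets the result.

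**Precision of the all-event comparison.** At 10% risk in both arms, the standard error of the difference is √(2 × 0.1 × 0.9 / 18) = 0.10. A 95% interval is therefore about ±1.96 × 0.10, or ±20 percentage points.

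**The case against.** The best defence is that this is a descriptive feasibility study of 36 people with no planned formal safety comparison. In the Outcomes section, the comparison with the booklet is attached to effectiveness, and safety is framed as safety of the intervention. The all-event comparison would itself be very imprecise, and with equal risks the false excess in the illustration is below one event. This stands, and it limits the weight of the point. It does not justify filtering by cause before counting, since few events are a reason to keep them all.

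Several stronger readings are tempting, and the document does not support them.

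- *Unblinded staff make the attribution.* This is an inference. All researchers are unblinded, but no assessor is named, and the full protocol may set out a procedure.
- *The control count is zero by definition.* It is not. The wording refers to participation in the study. Both arms undergo the sit-to-stand and grip tests at baseline and 12 weeks, and the leaflet also covers staying active. Qualifying control events would be rare, not impossible.
- *Control-arm events go unrecorded.* The article does not say so, and the Abstract's broader wording points the other way.
- *Falls will be explained away.* That is a risk of the definition, not something the document says will happen.
- *The halting provision depends on this count.* Ethical Considerations does not tie the two together.
- *Upper limits after zero events show the cost of dropping control data.* The one-sided 95% limits are right: 1 − 0.05^(1/18) = 15.3% for 18 people and 1 − 0.05^(1/14) = 19.3% for 14. They describe one arm only and are the same whether or not control events are counted.

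**Conclusion.** The point holds as a defect in a stated definition, not as a complaint about missing detail. The article gives two descriptions of its safety outcome, and the more specific one makes the count depend on a causal judgement that is likely to differ by arm. Followed as written, it would rarely admit control-arm background events such as falls, so even a descriptive table by arm would not be a valid randomised comparison.

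Under the assumed risks and attribution rates, the rule produces a false excess of 0.23 to 0.90 events at equal risks of 5% to 10% (no attribution in controls). It counts anywhere from none to all of a true excess of 1.8 events when the risk doubles from 10% to 20%. The rates are illustrative. The conclusion needs only that attribution differs between the arms, which the difference in what they are asked to do and the lack of blinding make likely.

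The importance is moderate: safety is a secondary, descriptive outcome in a small trial. It would go too far to conclude that the arms cannot be tabulated side by side, or that the plan discards control-arm data.

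**What to change.** Reconcile the Abstract and the Outcomes section on one definition. Suggested wording for Outcomes: *All adverse events, including falls and injuries, will be recorded in both arms with the same prompt, regardless of cause. They will be tabulated descriptively by arm as number of events and number of participants with at least one event. Relatedness to participation will be given in a separate column.*

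The judgement of relatedness is kept, as a label on each event and no longer as a condition for counting it. With about 18 per arm, the text should also say that the comparison is imprecise and will be reported descriptively only.

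The cost is one item on the follow-up case report file, which all participants already complete, one more table column, and slightly more events to log. The Abstract states that data collection began in March 2024, so the change would go through the ethical amendment process that the article describes. No treatment or clinical rule changes.

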**Figure 1 figure1:**
[figure not shown]
Schedule of enrollment, interventions, and assessments.

### Sample Size

As this is a feasibility study that is not designed to detect statistically significant differences in measures, no formal power calculation has been conducted to determine the sample size. Lancaster et al [22] recommend a sample size of 36 participants for feasibility and pilot studies, so after accounting for potential dropout (at 20%), we aim to recruit 18 participants in each arm.

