### Outcomes

Primary outcomes will be related to feasibility and will assess engagement with the intervention, recruitment and retention rates, and acceptability of the intervention and study design. These findings are important to inform the development of a large-scale RCT in community-dwelling older adults to compare the effectiveness of KOKU-Nut to an information booklet about healthy living. Recruitment rates will be assessed as cumulative recruitment against the target rate each month. Retention rates will be calculated as the number of participants who completed the study divided by the number of participants randomized. Engagement with the intervention will be based on self-reported use of KOKU-Nut at the end of the 12 weeks (every day, 3-4 times a week, 1-2 times a week, and once or twice a month). A questionnaire previously developed and used by the research team for the KOKU app will assess the acceptability of KOKU-Nut [13]. Intervention acceptability will also be assessed using the 11-item, 7-point, modified Treatment Evaluation Inventory [20]. Higher scores indicate higher acceptability, with a score of 44 indicating moderate acceptability. Interviews will explore the acceptability of the intervention and the perceived impact of taking part in the study. Interviews will also consider the participant’s experience of the recruitment process, the assessment tools used, and their experience and motivation for participating in the study (positive and negative).

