## Results

We anticipate recruitment will commence in March 2024 and will continue until enrollment is complete (N=36). The analysis is expected to be completed by November 2024, and the results will be published by January 2025.

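### The sample size section says a 20% dropout allowance was made, but the recruitment target of 36 equals the recommended 36, so none was added

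*Protocol article*

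**What the plan says.** The Sample Size section states that no formal power calculation was done, because the study is not meant to detect statistically significant differences. It then rests the size on a cited recommendation of "a sample size of 36 participants for feasibility and pilot studies" and concludes: "so after accounting for potential dropout (at 20%), we aim to recruit 18 participants in each arm".

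Other sections show what the 36 counts. The Abstract says "We plan to recruit a total of 36 community-dwelling older adults using purposive sampling", with 1:1 allocation, and the Results section has recruitment running until 36 are enrolled. So 36 is the number entering the trial, not the number finishing it. The Outcomes section fixes the retention denominator: "Retention rates will be calculated as the number of participants who completed the study divided by the number of participants randomized".

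The Outcomes and Statistical Analysis sections say that means, SDs and Cohen d from this study will be used to size the future powered trial.

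**The concern.** A dropout allowance should make the number recruited larger than the number wanted with data. Here the recommended number and the recruited number are both 36, although the sentence says that a 20% loss lies between them. A reader would take it that the recommended size is protected against dropout, when the figures given provide no such protection.

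This sentence is the article's only justification of the sample size. The quantities at stake are those that need a 12-week measurement: pre-post changes in health measures, the SDs of those changes, and Cohen d. The usability and acceptability ratings of the app are also collected at the end of the 12 weeks, and only the intervention arm receives the app.

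**Working it through.** **Inputs**

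- Recommended size: 36 in total (Sample Size).
- Dropout assumed: 20% (Sample Size).
- Recruitment target: 18 per arm, two arms (Sample Size); 36 in total (Abstract, Results).
- Allocation: 1:1 (Abstract, Study Setting).

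**1. The plan's figure.** 2 x 18 = 36. This equals the recommended 36, so the implied inflation factor is 36/36 = 1.00.

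**2. The figure with the allowance applied to the stated base.** With dropout d, the number to recruit is N/(1 - d).

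- Total: 36/(1 - 0.20) = 36/0.80 = 45.
- Per arm: 18/0.80 = 22.5, rounded up to 23, so 46 with equal arms.
- The cruder form N x (1 + d): 36 x 1.20 = 43.2, rounded up to 44.

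Neither form gives 36 from a base of 36.

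**3. What 36 recruited implies.** Expected number with 12-week data = N x (1 - d).

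- Total: 36 x 0.80 = 28.8, about 29, which is 7 fewer than 36.
- Per arm: 18 x 0.80 = 14.4, so 14 to 15.

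**4. Which outcomes this touches**

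| Outcome | Number it rests on |
|---|---|
| Recruitment rate | all 36 enrolled |
| Retention rate | all 36 randomised (the denominator) |
| Baseline means and SDs | everyone measured at baseline |
| Change scores, their SDs, Cohen d | about 29 (14 to 15 per arm) |
| App usability and acceptability ratings | about 14, intervention arm only |

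**5. Size of the effect on Cohen d.** For an effect near zero, the standard error of d is approximately the square root of 2/n, with n per arm.

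- n = 18: square root of 2/18 = 0.33.
- n = 14.4: square root of 2/14.4 = 0.37.
- Ratio: square root of 1/0.80 = 1.12, so about 12% wider.

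**6. Precision for retention at N = 36.** If 29 of 36 are retained (80.6%), the Wilson 95% interval is about 65% to 90%.

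**The case against.** The strongest defence is that 36 is the recommended number to enrol, with a 20% loss regarded as tolerable within it. The section does not say whether the recommendation counts participants enrolled or participants with data, and the cited source is not available here. This part stands: the documents do not show that the trial falls short of the recommended size. A reader might infer such a shortfall from 29 against 36, but that follows only if the recommendation means completers. The defence does not save the sentence, however. If dropout is merely tolerated, it has not been accounted for in the target.

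A second defence is that 36 already contains an allowance on a smaller, unstated base. That is arithmetically possible: 14 per arm gives 14/0.80 = 17.5, rounded up to 18. So it would be wrong to infer that 36 cannot be a correctly inflated number. But no such base appears in the article, which names 36 as its starting point. On this reading too, about 29 would be expected to finish.

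A third objection concerns impact. A reader might infer that all the feasibility results rest on 29 participants. They do not: recruitment and retention use all those enrolled or randomised, baseline SDs use everyone measured at baseline, and the Recruitment section plans to contact dropouts for their reasons. No error rate, power or stated precision target depends on the allowance. This objection stands and limits the weight of the point.

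**Conclusion.** The statement that the target accounts for dropout is wrong as written: relative to the only base the article gives, the allowance added is zero. The gap is 9 participants (45 against 36), or 10 with equal arms. Equivalently, about 7 fewer participants than 36 would have 12-week data.

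The figure of about 29 is not stated in the plan. It follows from the plan's own 20%, assuming that the loss is equal in the two arms and that a dropout provides no 12-week data.

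The consequence is modest and confined to the 12-week change scores and effect sizes, and to the app ratings from about 14 intervention-arm users. It should be fixed because this is the sole sample size justification and those outputs are meant to inform the next trial. It does not call the design or the feasibility aims into question.

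**What to change.** Keep N = 36 and reword the end of the Sample Size section, for example: 36 participants (18 per arm) will be randomised; with 20% dropout, about 29 (14 to 15 per arm) are expected to have 12-week data. Delete the claim that dropout has been accounted for. Optionally, add the precision that 36 gives for retention: 29 of 36 retained would carry a 95% interval of about 65% to 90%.

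If the sponsor does want 36 participants with 12-week data, the alternative is to recruit 45 (46 with equal arms) and change the Abstract, Sample Size and Results sections to match.

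The first option costs one sentence, with no extra participants, time or change of analysis. Its only price is that the stated number with follow-up data becomes less favourable. The second adds 9 or 10 participants.

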### Recruitment

Men and women aged 65 years and older living independently in the community will be recruited through purposive sampling via local age UK groups, assisted living facilities, and university networks. We plan to recruit a mixture of participants with and without access to a tablet computer to explore differences in the outcomes and the experiences between those with and without prior experience with tablets or iPads.

The study will be advertised using social media, posters, and through current collaborations with sheltered housing facilities, local charities, and community-based organizations across Greater Manchester. Staff at assisted living facilities, charities, and community organizations will act as gatekeepers and will offer potential participants flyers about the study and participant information sheets. Older adults who are interested in participating can agree to have their details passed over to the research team (CF) and will complete the consent to contact form. The research team will follow up with participants who are interested in joining the study and screen potential participants. Alternatively, potential participants may contact the research team directly following the study advertisement in posters and on social media to find out more information and check their eligibility. An existing research database will also be used where older adults have previously consented to be contacted about future research. Participants on the research database will be contacted directly by the research team with the participant information sheet and summary of the research according to their preferred choice (via email, telephone, or letter). The research team will then arrange to conduct an initial telephone screening over the phone to determine eligibility, provide further information about the study, and answer any questions.

Recruitment for the qualitative interviews will be done purposefully, to recruit a demographically representative group of participants. To do this, the sample frame will be divided into a number of smaller groups, namely the treatment group, age, gender, and prior ownership of a tablet or iPad. Individuals will then be drawn at random from each of these groups. We also plan to contact any dropouts to understand their rationale for dropping out to optimize the retention of participants if continuing to a full RCT. Researchers will use the concept of information power [23] to determine the number of interviews, but we anticipate sufficient data will be obtained from interviewing 20% of participants recruited for the study. Figure 2 represents the overall flowchart of participants through the study.

Participants who meet the screening criteria and are interested in taking part will provide informed written consent (Multimedia Appendix 1) before being formally enrolled in the study. During the screening phone call, the researcher (CF) will arrange a date and time suitable for the participant to conduct the initial baseline assessment. Prior to completing baseline measures, participants will be randomized in a 1:1 ratio to receive the intervention (KOKU-Nut) or to the control group and receive usual care.

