### Data Collection Methods

#### Overview

All participants will receive in the post a baseline case report file to be completed before the baseline assessment to collect sociodemographic information including age, gender, ethnicity, marital status, occupation, use of digital technology, shopping, and cooking habits. Participants will also be asked to complete a 3-day food diary using Intake24 prior to the baseline visit [25]. This web-based dietary assessment tool is compliant with the general data protection regulations (2018), and participants will be sent a unique number that will enable the researcher to identify the digital dietary records. Data collected will be used to assess the consumption of different food groups to identify adherence to the Eatwell guide [14]. During the home visit, the researcher (CF) will collect baseline measurements to assess anthropometry, dietary intake, physical function, quality of life, mood, and frailty. All measurements are responsive to change, appropriate for use in this population, and easily assessed in a community setting.

At the end of the 12-week intervention period, all baseline measures will be repeated, and participants will complete a follow-up case report file to collect feasibility outcome data. The researcher will conduct one-to-one semistructured interviews with a selected group of participants from both the intervention and the control group. Interviews will be conducted in person or over the phone depending on the preference of the participant. Interviews will last approximately 60 minutes, will be audio-recorded, and then transcribed verbatim by the research team. Additional consent will be collected prior to conducting the interview. A topic guide developed for the study will be used flexibly to guide the interviews.

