### Statistical Analysis

All quantitative data will be analyzed in STATA (version 15; StataCorp). The primary outcome will be calculated with regard to the indicators of feasibility to investigate engagement with the intervention, recruitment and retention rates, and acceptability of the intervention and study design. These will be summarized appropriately using descriptive statistics including percentages, mean with SDs, and ranges. Pre-post intervention changes in health measures will be analyzed in an exploratory fashion to gain preliminary insights into the number of valid versus missing data and to assess how outcomes are associated with group assignment and intervention engagement. Effect sizes will be determined using Cohen *d* to calculate sample sizes for a powered RCT.

Qualitative interview transcripts will be managed using NVivo software (version 12; QSR International Pty Ltd) and analyzed using an inductive approach with the 5 stages of framework analysis [34,35] to understand any barriers to the recruitment process, the suitability of the assessment measures, and the practicality of using the KOKU-Nut intervention. The first stage of framework analysis involves familiarization of the data from the transcripts and audio-recordings. The second stage involves classifying the data into codes and identifying a thematic framework from the key themes identified. The third stage involves systematically indexing the data using the framework identified. The fourth stage involves charting and synthesizing the data to categorize and capture key concepts and themes. The final stage involves the mapping and interpretation of the data [34]. All stages of the analysis process will be discussed and reviewed with at least 2 researchers (ES and SB) to ensure rigor [36].

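### Interview sampling ignores app use, so participants who stay in the study but stop or barely use KOKU-Nut may, by chance, not be interviewed

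*Protocol article*

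**What the plan says.** The protocol article (Methods, Recruitment) chooses interviewees purposively, "to recruit a demographically representative group of participants". It divides the sampling frame by four factors, "namely the treatment group, age, gender, and prior ownership of a tablet or iPad", and continues: "Individuals will then be drawn at random from each of these groups". The wording presents the four factors as the whole list, and no other section adds level of app use as a criterion.

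One further group is reached: "We also plan to contact any dropouts to understand their rationale for dropping out". The stated reason is to improve retention in a later full trial.

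The number of interviews is to be settled by information power, and "we anticipate sufficient data will be obtained from interviewing 20% of participants recruited for the study". The Overview of Data Collection Methods places the interviews at the end of the 12 weeks, with "a selected group of participants from both the intervention and the control group". It does not say when interviewees are selected.

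Under Outcomes, engagement and acceptability both belong to the primary feasibility outcomes, and interviews are one source on acceptability. Engagement is self-reported at 12 weeks in four categories, from daily use down to once or twice a month. Under Statistical Analysis, the interview analysis is to cover, among other things, "the practicality of using the KOKU-Nut intervention".

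**The concern.** The sampling rule serves demographic spread, while the interviews are also meant to explain how workable and acceptable the app is. The people who know most about why it did not work are those who were given it and stopped, or hardly used it.

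The separate contact with dropouts does not reach them all. Retention is defined by completing the study, so a participant who abandons the app but completes follow-up counts as retained. That person is interviewed only if the random draw happens to pick them.

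Low use is foreseeable. The Introduction reports that existing users of the parent KOKU app average 2.2 sessions a week, and the Interventions section asks for at least 3.

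At stake is the qualitative evidence on barriers, which is to guide changes before a powered trial. If every app-arm interviewee were a regular user, that evidence would say little about why others stopped.

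**Working it through.** The plan states no figure for this risk, so there is none to reproduce. The check asks how often the written rule would miss every low user.

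**Inputs from the protocol article**
- Sample size: "we aim to recruit 18 participants in each arm", so 2 × 18 = 36 in total.
- Anticipated interview share: 20% of those recruited (Recruitment).
- Dropout allowance: 20% (Sample Size).

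**Assumptions not in the document**
- Interviews are split evenly between arms.
- There are *k* low or stopped users among the app-arm completers; *k* is varied.
- Everyone invited accepts.
- The draw is simple random with respect to app use, since use is not a stratum.

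**Step 1: number of interviews.** 0.20 × 36 = 7.2, about 7. Half of that is 3.6, so 3 or 4 in the app arm.

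**Step 2: app-arm completers.** 18 × (1 − 0.20) = 14.4, about 14.

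**Step 3: chance that no low user is drawn.** With *n* completers, *k* low users and *m* app-arm interviews, the chance is C(*n* − *k*, *m*) / C(*n*, *m*). For *n* = 14:

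| Low users *k* (assumed) | *m* = 3 | *m* = 4 |
|---|---|---|
| 2 | 220/364 = 60% | 495/1001 = 49% |
| 4 | 120/364 = 33% | 210/1001 = 21% |
| 6 | 56/364 = 15% | 70/1001 = 7% |

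If nobody dropped out (*n* = 18) and *k* = 4, the chance is 364/816 = 45% with 3 interviews and 1001/3060 = 33% with 4.

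**Step 4: can the existing strata close the gap?** Even with two levels per factor, four factors give 2⁴ = 16 cells for about 7 interviews. Most cells cannot supply an interviewee, so the demographic strata cannot be relied on to bring in low users indirectly.

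**Step 5: with app use as a criterion.** If at least one low user is selected, the chance of interviewing none falls to 0 whenever such a person exists and consents.

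**The case against.** The best defence is that this is a choice between reasonable sampling frames. The plan says it wants demographic representativeness, and its factors serve that. Prior tablet ownership also bears on likely difficulty with the app, and Recruitment states an interest in how experiences differ by it. Nothing is misstated or contradictory. This stands, and it is why the point is minor.

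Several things also limit the harm. Information power lets the number of interviews grow, so 7 is an expectation and not a ceiling. Acceptability is also measured by a questionnaire and by the modified Treatment Evaluation Inventory, and usability by its own scale. Nothing confines these to interviewees. With 4 low users of 14, at least one would be interviewed in 67% (3 interviews) to 79% (4 interviews) of draws. The highest chances of missing them arise when low use is rare. All of this stands too, but the questionnaires do not give low users' reasons in depth, and nothing in the plan directs extra interviews to them.

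A reader might go further and infer that barriers to use will be missed, or that the acceptability conclusion will be too favourable. The document does not support that: low users can be drawn by chance, and other acceptability data exist. Nor can one assume that app use is already known when interviewees are chosen. The interviews follow the 12 weeks, but the time of selection is not stated, and all four listed factors could be known at baseline.

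**Conclusion.** The point holds as a risk. The rule leaves to chance whether anyone who stayed in the study but stopped or barely used KOKU-Nut is interviewed, and contact with dropouts does not cover such people. With 14 app-arm completers and 3 to 4 interviews, the chance of hearing from none is 21% to 33% if there are 4 low users and 49% to 60% if there are 2. It falls to 7% to 15% if there are 6.

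These figures are illustrations. They rest on the assumed counts of low users, an even split between arms, full acceptance and a draw unrelated to app use. Interviews are optional, so if low users decline more often than others the risk is higher. If low means anything under 3 times a week, the group may be large and some will probably be drawn. The more exposed people are those who stopped or used the app once or twice a month.

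This is a cheap improvement to a stated rule, of minor severity, and not an error in the plan.

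**What to change.** In the Recruitment section, for the app arm only:

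- Add self-reported use at 12 weeks as a purposive sampling criterion, split into below versus at or above the requested 3 times a week. The split falls between two existing response categories.
- State that app-arm interviewees are selected after that response is known.
- Aim for at least one low or stopped user, where one exists and consents. A larger fixed quota would take too much of 3 to 4 places and work against the aim of representativeness.

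Under Outcomes, add a stopped/not used response to the engagement question. The lowest listed category is once or twice a month, so people who stopped cannot now be identified from it.

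Keep the number of interviews and the four existing factors. The cost is a short addition to the sampling text and one response option, with no extra visits or interviews. The downsides are slightly less demographic spread and the possibility that low users decline.
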